#### Intervention group

2.4.4

*Single-cycle measurement and adjustment strategy.* In participants randomized to the intervention group, a single-cycle measurement and adjustment strategy will be applied. Participants will have their blood drawn as soon as possible after inclusion (but no earlier than 3 days after initiation of a DOAC) to measure a first peak DOAC level (2-4 hours after intake). The following scenarios can occur (Figure 2):(1)First peak DOAC level is within the on-therapy range → a second peak DOAC level will be measured 1 week later → the second peak DOAC level is again within the on-therapy range → no adjustment is necessary, and participant continues to follow-up.(2)First peak DOAC level is outside the on-therapy range → dose adjustment or switch to another DOAC if dose adjustment within an approved dose range is not possible → a new first peak DOAC level will be measured 1 week later, after which 1 of the 3 scenarios described will be reassessed. This process could potentially continue indefinitely; however, 2 primary rules will be applied—except in the case of rivaroxaban (Supplementary Figures), as literature indicates a higher incidence of bleeding complications are associated with its use. The 2 primary rules are as follows: (1) dosage adjustments are permitted only once, and (2) switching to an alternative DOAC is allowed only once. For each DOAC, including each specific dose, a Standard Operating Procedure (SOP) has been established (Supplementary Figures). These SOPs include a flowchart outlining the adjustments to be made based on specific DOAC levels.(3)First peak DOAC level is within the on-therapy range → a second peak DOAC level will be measured 1 week later → the second peak DOAC level is outside the on-therapy range → further DOAC management will be discussed in a multidisciplinary team consisting of experts in anticoagulant management.

**Figure 2 fig2:**
[figure not shown]
Timeline of our single-cycle measurement and adjustment strategy. DOAC, direct oral anticoagulant; RCT, randomized controlled trial.

Based on the literature (Beers criteria [23]), we have specified apixaban and edoxaban as our first-choice DOACs in our SOPs. In circumstances in which initiating a participant on a DOAC is unsuccessful, ie, a participant has deviant DOAC levels after an adjustment has been made and after an individual treatment plan of the multidisciplinary team has failed, we will recommend the patient to switch to a VKA.

Importantly, in cases in which the DOAC level is not measurable or very low, we will first address therapy compliance with the participant, and a second DOAC level measurement will be performed before considering dose adjustment or switching to another DOAC.

*DOAC level measurement.* Blood sample analysis will be performed using commercially available and validated tests. For the measurement of DOAC levels, the following procedure will be followed. First, verification will be carried out to ensure that the DOAC was taken 2 to 4 hours prior to the blood sample collection. Blood will be drawn with minimal stasis in a 3.2% citrated vacuum tube (Becton Dickinson) via a puncture of the antecubital vein. Blood will be centrifuged in a 2-step procedure. First, it will be centrifuged for 5 minutes at 2500*g* at room temperature. For the second step, plasma will be centrifuged for 10 minutes at 10,000*g* at 18 °C. The Diluted TT Hemoclot test will be used for the measurement of dabigatran levels, and activated factor X (FXa) activity for the measurement of apixaban, rivaroxaban, and edoxaban levels (both Hyphen Biomed). More in detail, we will be using a clotting activity assay on the CS2500 Analyzer (Sysmex/Siemens), which employs a chromogenic substrate. This assay is the most widely used method globally to measure DOAC levels. It is ISO-15189 certified and registered under the In Vitro Diagnostic Regulation. This anti-FXa assay measures the effect of the DOAC and its active metabolites in relation to an excess FXa. The chromogenic substrate in the assay is cleaved by the residual FXa. Variations in active metabolites, which may be influenced by factors such as renal function disorders, are also assessed through this activity assay. Any shifts in the metabolite ratio will be reflected in the FXa activity measurement.

Dabigatran, apixaban, rivaroxaban, and edoxaban calibrators and assay controls will be obtained from Hyphen Biomed. All measurements will be performed according to the manufacturer’s instructions without modifications. Further, time from the last DOAC intake to time of blood draw will be recorded and, to interpret the DOAC level, we will use expected on-therapy ranges for peak plasma levels, defined as DOAC level measured within 2 to 4 hours after intake.

*Rationale for the use of DOAC peak plasma levels.* In the present study, we have opted to base our single-cycle measurement and adjustment strategy on DOAC peak plasma levels for several reasons. First, given our objective to reduce complications associated with DOAC use in the frail older population—who are particularly susceptible to bleeding risks, as shown by studies such as the FRAIL-AF trial [5]—deviant DOAC peak plasma levels are closely related to the risk of bleeding and thrombosis [11,12]. Second, as one of the primary advantages of DOACs is the absence of routine monitoring requirements, we sought to design a strategy that minimizes the need for intensive monitoring. As a result, we have chosen to measure only 1 DOAC level (peak), rather than both trough and peak plasma levels. This approach not only simplifies the strategy but also reduces the burden on patients, as it requires only a single blood sample. Finally, by limiting the strategy to peak-level measurement, we are able to reduce associated costs, further enhancing the feasibility of our strategy.

*DOAC peak-level interpretation.* For the DOAC peak-level interpretation, we will use the data (expected on-therapy ranges) recommended in the antithrombotic guidelines of the Federatie Medisch Specialisten in the Netherlands [24]. These expected on-therapy ranges are in line with data published by Douxfils et al. [25]. The Table shows the expected therapeutic ranges of peak DOAC levels as we will use them in the DOAC-FRAIL RCT.

**Table tbl1:** Expected on-therapy ranges of peak DOAC levels for atrial fibrillation and venous thromboembolism.

DOAC		Tmax (h)	Expected range	
			Lower limit (ng/mL)	Upper limit (ng/mL)
Apixaban, 5 mg	2 times daily	3-4	59	302
Apixaban, 2.5 mg	2 times daily	3-4	30	153
Edoxaban, 60 mg	1 time daily	1-2	125^a^	317^a^
Edoxaban, 30 mg	1 time daily	1-2	55^a^	225^a^
Rivaroxaban, 20 mg	1 time daily	2-4	177	361
Rivaroxaban, 15 mg	1 time daily	2-4	134^b^	278^b^
Rivaroxaban, 10 mg	1 time daily	2-4	91	195
Dabigatran, 150 mg	2 times daily	0.5-2	60	450
Dabigatran, 110 mg	2 times daily	0.5-2	80	300

All expected on-therapy ranges are based on data published in the antithrombotic guidelines of the Federatie Medisch Specialisten in the Netherlands. They are in line with data published by Douxfils et al. [25].

DOAC, direct oral anticoagulant.

a As no data is available on the expected therapeutic ranges for edoxaban, we will use the expected therapeutic ranges established by the laboratory of Maastricht University Medical Center (MUMC+).

b Since there is no available data on the expected range for rivaroxaban 15 mg, we will use the average of the therapeutic ranges for rivaroxaban 20 mg and 10 mg.

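### The dabigatran lower limits in the Table of peak ranges run opposite to dose (80 ng/mL on 110 mg, 60 ng/mL on 150 mg) without explanation, so at least one treatment trigger is probably wrong.

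*Protocol article*

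**What the plan says.** Section 2.4.4 (Intervention group) of the protocol article describes a strategy in which a first peak level outside the on-therapy range leads to "dose adjustment or switch to another DOAC if dose adjustment within an approved dose range is not possible". Two rules cap the process for every drug except rivaroxaban: "dosage adjustments are permitted only once" and "switching to an alternative DOAC is allowed only once".

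The limits come from the Table in the same section. The text leaves no doubt that they are operative: "The Table shows the expected therapeutic ranges of peak DOAC levels as we will use them in the DOAC-FRAIL RCT". For dabigatran the rows are:

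- "Dabigatran, 150 mg 2 times daily 0.5-2 60 450"
- "Dabigatran, 110 mg 2 times daily 0.5-2 80 300"

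The last two figures in each row are the lower and upper limits in ng/mL. The general note under the Table gives the origin: "All expected on-therapy ranges are based on data published in the antithrombotic guidelines of the Federatie Medisch Specialisten in the Netherlands". It adds that they agree with a second published source. Footnotes explain the edoxaban rows (local laboratory ranges) and the rivaroxaban 15 mg row (an average). There is no footnote on dabigatran.

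The article also states: "For each DOAC, including each specific dose, a Standard Operating Procedure (SOP) has been established". Those flowcharts are in supplementary figures that are not available here.

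**The concern.** A lower dose of the same drug, taken equally often, would be expected to have a lower limit no higher than that of the larger dose. Dabigatran has the reverse. The limits define when the experimental strategy acts, so the order matters for treatment.

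There are two possibilities if one entry is wrong. If 80 ng/mL on 110 mg is too high, some users of 110 mg are flagged as low when they are not. They may then use up their one permitted dose adjustment, or their one permitted switch if the SOP directs one. If 60 ng/mL on 150 mg is too low, some low peaks on 150 mg pass as acceptable and no action follows.

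The same limits would define the prevalence of deviant levels and the deviance indicator in the logistic model (section 2.5). The linear model of actual levels does not use the cut-off.

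**Working it through.** **Inputs.** All are limits in ng/mL from the Table in section 2.4.4.

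**Reproducing the plan's own figure.** The only row whose derivation is given is rivaroxaban 15 mg, stated to be the average of the 20 mg and 10 mg ranges. Lower: (177 + 91)/2 = 134. Upper: (361 + 195)/2 = 278. Both match the printed 134 and 278, so the Table is being read correctly.

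**Order check.** For each pair of adjacent doses, ratio = value on the lower dose / value on the higher dose. A ratio below 1 means that the limit falls as the dose falls.

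| Pair | Dose ratio | Lower-limit ratio | Upper-limit ratio |
|---|---|---|---|
| Apixaban 2.5 / 5 mg | 0.50 | 30/59 = 0.51 | 153/302 = 0.51 |
| Edoxaban 30 / 60 mg | 0.50 | 55/125 = 0.44 | 225/317 = 0.71 |
| Rivaroxaban 15 / 20 mg | 0.75 | 134/177 = 0.76 | 278/361 = 0.77 |
| Rivaroxaban 10 / 15 mg | 0.67 | 91/134 = 0.68 | 195/278 = 0.70 |
| Dabigatran 110 / 150 mg | 0.73 | 80/60 = **1.33** | 300/450 = 0.67 |

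Five pairs with two limits each give ten comparisons. Nine ratios are below 1. The dabigatran lower limit is the only exception, and dabigatran's own upper limit falls with dose as expected.

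**Like with like.** Both dabigatran rows are twice daily, carry the same Tmax (0.5 to 2 hours), and are measured in this trial with the same diluted thrombin time assay. Nothing in the trial's procedures gives the two doses different scales.

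**Is it a reading error?** Both rows are complete and their other columns agree with each other, so a fault in text extraction is unlikely.

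**Consequence as printed.** Take a first peak of 70 ng/mL. On 150 mg, 70 is above 60 and below 450: in range. On 110 mg, 70 is below 80: out of range, with a change of dose or drug to follow. The same holds for every value from 60 to under 80 ng/mL. This band, 20 ng/mL wide (80 − 60), is all that the printed numbers establish.

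**The case against.** The strongest reply is that these are ranges expected in treated patients, not limits calculated from dose. The Discussion (section 3) says that levels depend on renal function, comorbidities, other medication, adherence and sampling time, and the Table covers both atrial fibrillation and venous thromboembolism. The two dabigatran rows could come from different populations or use different percentiles, and a guideline could print exactly these values. There would then be no transcription error.

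Part of this stands. The guideline is not at hand and the possibility cannot be excluded. But none of these explanations is given in the article. The authors annotated other unusual rows and left this one without comment. If users of 110 mg simply ran higher levels for their dose, the upper limit might be expected to move the same way, yet it drops by a third. Provenance also does not explain why 70 ng/mL should be acceptable on the larger dose and prompt a change on the smaller one.

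It is also fair that the SOPs, not shown, fix what happens to a particular patient. Levels that are unmeasurable or very low lead to a compliance discussion and a repeat measurement before any change. The article does not say whether 60 to under 80 ng/mL counts as very low. A repeat measurement would not correct a wrong cut-off.

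Some stronger readings are tempting but unsupported:

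- **That a particular cell is wrong, or that the two cells were exchanged.** An exchange would restore the order, but nothing in the article points to it over the alternatives.
- **That the affected band is wider.** Scaling limits with dose would give 60 × 110/150 = 44 ng/mL for 110 mg, or 80 × 150/110 = 109 ng/mL for 150 mg. That assumes proportionality, which the Table itself breaks: halving the edoxaban dose takes the lower limit to 0.44 and the upper to 0.71 of its value.
- **That the primary result is biased.** Participants are compared as randomised, whatever limits the strategy uses.

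**Conclusion.** The point holds as a minor one. The dabigatran lower limits are reversed relative to dose, without explanation, in a table of treatment triggers. At least one is probably wrong. That judgement assumes that the limits for two doses of one drug should not run against dose when drawn on the same basis. The other nine comparisons in the Table fit that assumption, but the article does not state it.

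The band at issue is 60 to under 80 ng/mL. The number of dabigatran users and the share of them in this band are not given, so the effect on the trial cannot be sized. It is likely to be small, since apixaban and edoxaban are the first-choice drugs in the SOPs. What is affected is the treatment of individual dabigatran users in the intervention group and the secondary analyses of deviant levels. The intention-to-treat comparison is not biased.

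**What to change.** Check both dabigatran lower limits against the cited guideline and against the dabigatran SOPs. Then:

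- **If either value was mis-transcribed,** correct it in the Table and the SOPs, and reclassify dabigatran participants already measured. The abstract says recruitment has begun, so an early check limits how many decisions are affected.
- **If the source prints the reversed values,** state the justification (for example different percentiles or populations), or use limits for both doses drawn on the same basis, before they serve as a treatment trigger.

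The limits should not be reordered merely to restore the pattern, before the source has been checked. The cost is a check of two table cells, followed by a corrected entry or a short explanatory note. Reclassification is needed only if a value changes.

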#### Control group

2.4.5

In participants randomized to the control group, standard care will be given. Standard care includes that the choice of type and dose of DOAC are left at the discretion of the treating physician. There will be no interference in the choice or dose of DOAC at study inclusion. Further, it is up to the attending physician to follow guidelines on follow-up (renal function, body weight, etc.), but we assume this will at least include the annual check.

Additionally, in a subgroup of participants (all participants included in the MUMC+) blood samples will be collected at the time of inclusion and stored for future analyses.

#### Assessments of study outcome(s)

2.4.6

For the primary outcome, bleeding will be assessed using the International Society on Thrombosis and Haemostasis Bleeding Assessment Tool [26], of which a modified version will be used in the follow-up visits. Thrombosis, more as safety endpoint, will be assessed through history taking. In addition, the EPR will be evaluated for adverse events.

For certain secondary objectives, the following questionnaires will be used as outcomes: EQ-5D-5L score, KATZ scale, and Lawton & Brody scale. Feasibility will be assessed through a qualitative study, including semistructured interviews with health care professionals and patients. Other secondary outcomes will be collected by anamnesis during the follow-up visits and reviewing the EPR (determinants of deviant DOAC levels, mortality). Finally, a cost analysis will be conducted to assess the balance between the additional costs associated with this strategy and the health care–related cost savings it may prevent.

**Figure 3 fig3:**
[figure not shown]
Timeline of the follow-up of the DOAC-FRAIL RCT. CRNM, clinically relevant nonmajor bleeding; EPR, electronic patient record; DOAC, direct oral anticoagulant; RCT, randomized controlled trial.

#### Follow-up visits

2.4.7

During the 2-year follow-up period of the study, participants will be contacted every 6 months by telephone (Figure 3).

During the telephone visit, the occurrence of bleeding or thrombosis will be evaluated and several questionnaires, as stated above, will be completed. Telephone visits are preferably conducted with the participant; alternatively, they may be conducted with a family member if necessary. For nursing home residents unable to complete questionnaires, a health care professional is contacted to assess, eg, occurrence of bleeding. In addition to these telephone visits, the EPR system will be consulted to identify/confirm the occurrence of complications and evaluate, eg, compliance.

Information on DOAC levels measured at the occurrence of a complication (bleeding/thrombosis) in the total research population will be collected through evaluation of the EPR. Nowadays, it is often standard care to perform a DOAC level measurement in such urgent medical situations in many academic hospitals.

In addition, evaluation of the EPR will be conducted to identify any (potentially) missing data and to gather information on changes in kidney function, medication, weight, and the standard care provided.

### Data analysis

2.5

After the first 100 patients in the intervention group have completed the single-cycle measurement and adjustment strategy, an analysis will be conducted to determine whether a second DOAC measurement is necessary, provided that the first DOAC measurement falls within the expected therapeutic range.

Baseline characteristics will be presented stratified by allocation. The primary analysis will be performed according to the intention-to-treat principle. In addition, a per-protocol analysis will be conducted. To evaluate whether the single-cycle measurement and adjustment strategy is superior to standard care with respect to the composite endpoint, a competing risks survival model according to Fine and Gray will be used to analyze time to first event, accounting for competing events. The effect of treatment will be expressed as hazard ratios with corresponding 95% CIs. The proportional subdistribution hazards assumption will be assessed using appropriate diagnostic methods. Recurrent events and their nature will be summarized descriptively. Depending on the distribution of event counts, additional analyses using Poisson regression may be performed to formally test differences in the number of events between groups.

Furthermore, the aforementioned analyses will also be conducted separately for new users and long-term users. In addition, subgroup analyses in participants aged > 70, > 80, and > 90 years will be performed. Last, participants requiring a switch to VKA will be excluded to perform subgroup analyses to evaluate the effect in participants who use a DOAC.

Two-sided *P* values < .05 will be regarded as statistically significant. Missing data will be imputed depending on the extent of missing data and the likely mechanism. Results will be expressed as odds/hazard ratios including 95% CIs.

Descriptive statistics will be used to present the prevalence of deviant DOAC levels. Logistic and linear regression analyses will be performed to estimate associations between potential predictors of deviant DOAC levels and actual levels (linear model) and a deviance indicator (logistic model). Mixed-effects regression models for repeated measures will be used to assess the effect of the intervention on quality of life over the course of follow-up. Fixed effects will be time, study group, their interaction, and a set of potential confounding variables.

The feasibility and acceptability of the single-cycle measurement and adjustment strategy will be evaluated within a qualitative study. A cost–utility study will be performed to evaluate the cost-effectiveness of our intervention. Health care consumption will be collected from the EPRs and linked to Dutch unit costs. Kaplan–Meier survival curves will be used to visually represent the survival experience of participants in the 2 groups. To formally test differences in survival rates, Cox proportional hazards regression will be performed, adjusted for potential confounders (such as age, sex, and comorbidities).

Additional explorative analyses will be performed after stratification for eg, DOAC, new users vs experienced users, and adjustments due to DOAC peak plasma levels above and below the expected on-therapy range.

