****Methods**:**

The DOAC-FRAIL study is an international, multicenter, randomized controlled trial including frail older patients aged ≥70 years with a Clinical Frailty Scale score >3 receiving DOAC therapy. Participants are randomized to either a Single Cycle Measurement and Adjustment Strategy based on peak DOAC plasma concentrations or standard care. Patients with a life expectancy of less than 3 months or previous DOAC dose adjustment based on plasma level measurements are excluded. The primary outcome is the composite of bleeding events, including clinically relevant non-major bleeding, and thromboembolic events during 2 years of follow-up. Secondary outcomes include feasibility, determinants of deviant peak DOAC plasma concentrations, quality of life, cost-effectiveness, and all-cause mortality

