### Sample size calculation

2.3

For the sample size calculation, we made the following assumptions. First, the risk reduction applies to the entire intervention group, as the intervention consists of a single-cycle measurement and adjustment strategy, irrespective of whether this leads to a dose adjustment or DOAC switch. Second, the yearly incidence of the composite endpoint is assumed to be 15% to 20% in the control group, based on the literature [14], and 10% to 15% in the intervention group, based on an estimated absolute reduction of 5% after the single-cycle measurement and adjustment strategy. With a 1:1 allocation and a 2-sided α level of 0.05, 686 to 905 participants are required in each treatment arm to have a power of at least 0.80. Considering a drop-out percentage of ∼10%, a total of 1509 to 1991 participants is required and will be included.

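### The primary analysis is repeated separately in new and long-term users under an unrestricted P < .05 rule, with no interaction stated and an unclear exploratory status

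*Protocol article*

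**What the plan says.** Data analysis (2.5) names one primary analysis: intention-to-treat, time to first composite event, Fine and Gray model, testing superiority. It then extends this to user status: "Furthermore, the aforementioned analyses will also be conducted separately for new users and long-term users". Age subgroups and a subset without participants who switched to a VKA follow. The next paragraph sets the threshold for two-sided P: "values < .05 will be regarded as statistically significant". Nothing ties that sentence to the primary analysis.

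The only interaction in the section is time by study group, in the quality-of-life model. At the end of 2.5 the user-status split returns under a different label: "Additional explorative analyses will be performed after stratification for eg, DOAC, new users vs experienced users".

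Two other sections bear on this. Randomization and blinding (2.4.2) makes new versus experienced use a stratification factor. Sample size calculation (2.3) sizes the trial for the overall comparison only: "With a 1:1 allocation and a 2-sided α level of 0.05", it states that "686 to 905 participants are required in each treatment arm to have a power of at least 0.80". I take long-term and experienced users to be the same group.

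**The concern.** For user status the article does not merely leave a detail open. It names a method, separate analyses in each stratum. A result below .05 in one stratum and above it in the other is not evidence that the effect differs, because the strata may differ only in size and therefore in power. Under the rule as written, one stratum would be called significant and the other not, and the natural reading is that the strategy works in one kind of user only.

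That reading bears on a practical question the trial will be asked to answer: whether levels should be measured when a DOAC is started, in established users, or in both. Because user status is a randomisation stratum, readers will give a stratum result more credence than an ad hoc subgroup. The two labels in 2.5 leave it open whether such a result counts as a planned finding or an exploratory one.

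**Working it through.** **Inputs from Sample size calculation (2.3).** Two-sided α 0.05, 1:1 allocation, power at least 0.80, 686 to 905 per arm. For control, "the yearly incidence of the composite endpoint is assumed to be 15% to 20% in the control group"; for the intervention, "10% to 15% in the intervention group, based on an estimated absolute reduction of 5" percentage points. The share of new users is not given, so I assume 10% to 50%.

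**The plan's own figure.** Comparing two proportions with pooled variance, n per arm = [1.960·√(2p̄(1−p̄)) + 0.842·√(p₁(1−p₁)+p₂(1−p₂))]² / (p₁−p₂)².
- 15% vs 10%: 685.6, so 686 (stated 686).
- 20% vs 15%: 905.4 (stated 905).

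The stated sizes reproduce, and they give power 0.80 for the overall comparison.

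**Same true effect in both strata.** The overall test statistic has mean 1.960 + 0.842 = 2.802. In a stratum holding a share f of the participants the mean is 2.802·√f, and power is approximately Φ(2.802·√f − 1.960). The strata are disjoint, so with stratum powers a and b, P(exactly one significant) = a(1−b) + b(1−a).
- 50/50: 2.802 × 0.707 = 1.981, so power is 0.508 in each; 2 × 0.508 × 0.492 = 0.50.
- 20/80: 2.802 × 0.447 = 1.253, power 0.24; 2.802 × 0.894 = 2.506, power 0.707; 0.24 × 0.293 + 0.707 × 0.76 = 0.61.

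Applying the two-proportion power formula directly to 686 per arm (15% vs 10%) gives the same picture. At 905 per arm (20% vs 15%) the results agree to within 0.001.

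| New users (assumed) | Power, new | Power, long-term | Exactly one significant | Both significant |
|---|---|---|---|---|
| 50% | 0.508 | 0.508 | 0.500 | 0.258 |
| 30% | 0.334 | 0.649 | 0.549 | 0.217 |
| 20% | 0.239 | 0.707 | 0.608 | 0.169 |
| 10% | 0.141 | 0.758 | 0.685 | 0.107 |

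**If true power is higher.** The sample size uses yearly rates, but follow-up is 2 years. Compounding without competing death gives 1 − 0.85² = 27.8% vs 1 − 0.90² = 19.0%, or 1 − 0.80² = 36.0% vs 27.8%, and overall power of about 0.97. Exactly one stratum is then significant in 0.35 to 0.37 (50/50), 0.58 to 0.59 (20/80) and 0.75 (10/90) of trials.

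**Global null.** P(at least one significant stratum) = 1 − 0.95² = 0.0975. In simulation, a user stratum is significant while the overall test is not in about 6% of trials, so about 3% in the direction of benefit.

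**The interaction test for comparison.** With the same effect in both strata it rejects in 5% of trials. Its power is low. The standard error of the between-stratum difference is the overall standard error divided by √(f(1−f)), that is 2.0 times at 50/50 and 2.5 times at 20/80. For a difference as large as the overall design effect, the mean is 2.802/2.0 = 1.40 (power about 0.29) or 2.802/2.5 = 1.12 (power about 0.20).

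**The case against.** The strongest reply is that this is a condensed article. Interaction tests and multiplicity rules are commonly left to a full protocol or SAP that is not shown, so their absence proves nothing. That stands for a testing order among the secondary outcomes, and I do not ask for one. It does not dispose of the user-status point, because here the article fixes a method, separate analyses, and that method cannot answer whether the effect differs.

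A second reply is that the closing list of explorative analyses may refer to the determinant, quality-of-life, cost and survival analyses described just before it, so that the composite endpoint does not carry two labels. The wording allows this. It also allows the other reading, so the status is unclear rather than flatly contradictory.

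Third, the harm needs someone to over-read the stratum P values, and the article does not propose to compare them. That is fair, but an unrestricted significance rule placed directly after the subgroup paragraph invites it.

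Three stronger readings are tempting and not supported:
- **Every secondary outcome is declared significant at .05.** The abstract lists them: "Secondary outcomes include feasibility, determinants of deviant peak DOAC plasma concentrations, quality of life, cost-effectiveness, and all-cause mortality". Under 2.5, feasibility is assessed qualitatively, the prevalence of deviant levels is descriptive, and the cost–utility study has no stated test. The threshold reaches only what is tested: predictors, quality of life and mortality.
- **False subgroup claims are likely.** A chance of 0.0975 is about twice the nominal rate. That is raised, not likely.
- **The trial's type I error is inflated.** There is one primary outcome and one primary intention-to-treat analysis at .05, and the stratum analyses do not touch it.

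**Conclusion.** The point holds in a narrow form. The separate tests by user status are the wrong tool for asking whether the effect differs, the P < .05 rule is not kept away from them, and the split's status in 2.5 is unclear. Discordant stratum results under an identical true effect are to be expected: about 50% (50/50) to 61% (20/80) of trials at the design power of 0.80, and roughly 35% to 75% over new-user shares of 50% to 10% if power is nearer 0.97. These figures rest on the assumed shares and on a common effect in both strata; the 35% to 75% range also rests on compounding the yearly rates without competing death. Analysing user status is itself legitimate, since it is a prespecified randomisation stratum. The amendment is worth making before results exist, but the validity of the primary result does not depend on it.

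**What to change.** In Data analysis (2.5):
1. Replace the separate composite-endpoint tests with one Fine and Gray model containing treatment, user status and their interaction.
2. Report the stratum-specific subdistribution hazard ratios with 95% CIs from that model, and base any statement that the effect differs on the interaction alone.
3. Give the user-status split one status, exploratory, both where it is introduced and in the closing list, and use the same name for the experienced group throughout.
4. State that the P < .05 significance rule does not apply to the stratum results.

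The cost is a few sentences and one model term on a variable already collected for randomisation; no participants or data are added, and the sample size is unchanged. Two things are given up. Nominal significance can no longer be claimed within a stratum. The interaction test also has low power, so a non-significant interaction must not be reported as proof that the effect is the same; the interaction estimate and its interval should carry the message.
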